## Abstract

Ecological momentary assessment (EMA) enables the collection of real-time data on individuals’ feelings, behaviors, and contexts through repeated short assessments, typically delivered via smartphones. Despite its value for understanding everyday determinants of well-being, EMA is less commonly implemented than traditional, retrospective self-report methods in many applied and community-based research settings, in part because of the participant burden it can impose. This study protocol describes a randomized controlled trial designed first to estimate invitation-stage willingness to participate in an explicitly described smartphone-based EMA study recruited through a public community platform, and second to evaluate whether scalable financial and social incentives increase this willingness in this setting. Specifically, the study investigates how a lottery-based financial incentive and a non-financial social incentive influence willingness to participate (Yes/No) in an explicitly described EMA study focused on the impact of urban environments on subjective well-being. It also examines reasons for non-participation among those unwilling to participate, as well as alternative incentive preferences that could motivate future participation. The study targets 4,809 users of a digital community platform for residents, workers, and visitors in King's Cross, London. Using a stratified block randomization procedure with randomly permuted block sizes, participants are allocated to one of three conditions: a financial incentive (prize draw for shopping vouchers), a social incentive (invitation to a study feedback event), or a control condition (no incentive). Randomization is stratified by residential status. Invitations describing the EMA study in the neighborhood are sent to user email addresses and willingness-to-participate responses are collected through a brief follow-up questionnaire. Logistic regression will test differences across groups, while secondary analyses will explore subgroup variations by age, gender, and residential categories, as well as reported reasons for non-participation and preferred incentive alternatives. This trial is expected to provide evidence on invitation-stage willingness to participate and on the effectiveness of scalable financial and social incentives for promoting participation in EMA-based well-being research. Together with insights into reasons for non-participation and preferred incentive alternatives, these findings will inform scalable approaches to public engagement with smartphone-based EMA in health and well-being studies.

## Introduction

1

Subjective well-being (SWB) refers to how people experience and evaluate their lives and specific domains and activities in their lives. Interest in SWB has gained increasing attention across economic, social, and health research because it provides insight into the conditions under which people live and can inform policy decisions in these domains (1–3). SWB includes both evaluative and affective dimensions: evaluative SWB concerns people's overall assessments of their lives, typically through life satisfaction, whereas affective well-being concerns the feelings, emotions, or states they experience over time (3). While overall life satisfaction provides an important global assessment, SWB is also shaped by short-term dynamics and by the context in which people live, work, and move. In particular, affective SWB is inherently dynamic and context-dependent, which creates a need for research approaches that can measure lived experience as it unfolds in everyday life rather than relying solely on retrospective self-reports (4, 5).

Ecological Momentary Assessment (EMA), also referred to as the Experience Sampling Method (ESM), is one such approach to capture momentary changes in SWB (6, 7). EMA is a self-report data collection that uses signals (e.g., notifications) to prompt individuals to report their behaviors, moods, perceptions, and experiences in their natural environment (6–8). Participants are typically prompted on smartphones to complete brief questionnaires multiple times per day while engaging in their usual activities (8, 9). By capturing data in real time, EMA reduces recall bias common in traditional survey methods and enables the investigation of temporal associations and variability in experience as they naturally unfold (8, 9). Compared with global self-report measures of evaluative well-being, EMA is particularly well suited to assessing affective SWB because it captures moods and emotions in their immediate context (9). These features also make EMA especially useful for studying how neighbourhood environments relate to well-being. Growing evidence indicates that the built environment of local neighbourhoods influences residents’ well-being (10–12), and EMA offers a useful way of examining these relationships by capturing momentary affective SWB together with *in-situ* information on activities, perceptions, and environmental context (13, 14).

Despite these advantages, the successful implementation of EMA depends on individuals' willingness to participate in intensive, repeated self-reporting (15). Protocols that require frequent prompts, longer study duration, or longer questionnaires may be perceived as burdensome; evidence indicates that higher assessment intensity can increase perceived burden and reduce adherence or compliance (16–18). This matters not only for data completeness after enrolment, but also for who participates in the first place, as willingness to take part may vary systematically across individuals (15).

Incentives are commonly used in EMA studies to encourage participation. Evidence reviews of mobile EMA sampling describe several types of compensation structures, including fixed payments, response-contingent rewards, raffles or lotteries, and studies offering no reward (19). However, most empirical evaluations of incentives in EMA have focused on engagement after enrolment, such as prompt completion or compliance, rather than on initial uptake at the invitation stage (20, 21).

Evidence on how study design features influence initial participation in EMA remains limited. One experimental vignette study found that higher guaranteed compensation increased reported willingness to participate in a hypothetical EMA study (22). While such designs provide useful insights into how potential participants evaluate study features, they rely on stated intentions rather than actual behavior. More recent research has examined participation using staged recruitment processes. For example, a population-based study documented substantial attrition across a postal recruitment funnel and showed that uptake varied when invitees were presented with protocols differing in burden (23). However, this does not reflect real-world digital health contexts in which invitations are delivered through apps or online platforms, and participation decisions are made in response to brief digital messages rather than multi-stage postal recruitment (23).

It is also important that recruitment strategies are feasible to implement at scale and under practical resource constraints. Evidence from survey methodology suggests that monetary incentives generally increase response rates more than non-monetary incentives, that prepaid incentives often outperform promised incentives, and that money may be more effective than vouchers or lotteries, although prepaid incentives may be difficult to administer in web-based surveys or recruitment contexts (24, 25). At the same time, lottery-based incentives are commonly used within EMA studies to sustain participant engagement after enrolment, as they provide a salient reward while lowering expected marginal costs (19). Whether such incentives also influence individuals' initial decisions to participate, however, remains less clear.

Non-financial strategies may also encourage participation, particularly in community-based research where reciprocity and shared benefit—such as providing feedback on study findings—may motivate engagement. Behavioral theories suggest that different incentives may appeal to different motivations, including financial rewards, topic relevance, or perceived community benefit (26, 27). However, there is limited empirical evidence on whether such non-financial incentives are effective in improving participation in EMA studies.

To address this evidence gap, this study will evaluate the effectiveness of two scalable incentive strategies—a lottery-based financial incentive and a community-framed non-financial incentive—in encouraging invitation-stage willingness to participate in a future EMA study among an urban neighbourhood population. A guaranteed payment incentive arm was considered but not included because the primary methodological question is whether implementable, lower-cost alternatives can improve recruitment in a community platform context. To ensure the study still informs this design space, we will also assess nonparticipants' stated preferences for alternative incentive structures, including guaranteed payments (see Supplementary File S1).

The study has five objectives:
To estimate the overall invitation-stage uptake for the proposed EMA study (i.e., the proportion of invitees who register interest) in this community recruitment context.To determine whether offering a financial incentive (eligibility for one of four £100 prize draws) or a social incentive (exclusive invitation to a neighbourhood social event for sharing study results) increases individuals’ willingness to participate in experience sampling research, compared with offering no incentive.To investigate whether the effectiveness of the incentives in promoting participation varies across demographic and residential subgroups, including residential status, age group, and gender.To examine the reasons provided for non-participation and assess whether the likelihood of endorsing specific reasons differs by incentive condition among those who declined participation.To identify which alternative incentives are most preferred by individuals who declined participation, and assess whether these preferences differ by the incentive condition originally offered.

## Methods

2

The study methods are reported in accordance with SPIRIT guidelines (participants, interventions, outcomes, randomization, data collection and management, analysis, and monitoring) (28).

### Study design

2.1

This is a three-arm superiority randomised controlled trial (RCT) that evaluates the impact of two types of incentives against a control condition on willingness to participate in EMA research among an urban neighbourhood population.

### Study setting

2.2

This study is conducted in the King's Cross, an urban neighbourhood in London, United Kingdom. The specific setting is the regenerated area within the King's Cross neighbourhood. The once derelict area has been transformed into a vibrant new part of London that currently has a mixed-use development with leisure and community facilities, shops, homes, offices, restaurants, bars, galleries, music venues, and an arts college. Table 1 presents the demographics of King's Cross neighbourhood.

**Table 1 T1:** 2021 census topic summaries, ONS © crown copyright. Created by: Insight & Improvement, Strategy Family, © LB Camden.

Demographics		Number	%
Ethnic Groups	White	4,617	45.4%
	Asian or Asian British	3,233	31.8%
	Black or Black British	985	9.7%
	Mixed/Multiple Ethnic Groups	717	7.0%
	Other Ethnic Group	628	6.2%
All Usual Residents Sex	Male	4,861	47.7%
	Female	5,322	52.3%
All User Residents Resident Type	Lives in a household	7,853	77.1%
	Lives in a communal establishment	2,328	22.9%
All User Residents (16+) Education	Level 4 qualifications and above	3,975	43.4%
	Level 3 qualifications	2,501	27.3%
	No qualifications	1,135	12.4%
	Level 2 qualifications	616	6.7%
	Level 1 & entry level qualifications	464	5.1%
	Other qualifications	284	3.1%
	Apprenticeship	179	2.0%
Age groups	15-24 years	3,502	34.4%
	25-44 years	2,972	29.2%
	45-59 years	1,446	14.2%
	60-74 years	910	8.9%
	5-14 years	644	6.3%
	0-4 years	332	3.3%
	75-84 years	278	2.7%
	85 + years	99	1.0%
Employees^a^	Full-time employees	15,000	71.43%
	Part-time employees	6,000	28.57%

a Employees are not necessarily residents in King's Cross. Some of them reside outside King's Cross. Furthermore, people could have more than one job. Data is retrieved from ONS Business Register and Employment Survey. From http://www.nomisweb.co.uk.

### Participants

2.3

The participants in this study are visitors, residents, and commercial occupiers in the regenerated area of King's Cross. Commercial occupiers could be classified as office occupiers or retail occupiers. Office occupiers have large office spaces in the neighborhood; examples are Google, Meta, Universal Music, PRS for Music, and Havas. Retail occupiers have smaller spaces, and they include independent stores, gyms, hair and beauty salons among others. Employees working in either office or retail occupiers are “commercial occupiers” and comprise the first category of participants in this study. The office-vs.-retail distinction is provided for descriptive context only; for the purposes of this study, all employees working for non-residential occupiers were grouped as “commercial occupiers.” Secondly, residents are household owner-occupiers, private renters, and social housing occupants in the neighbourhood. Lastly, visitors are individuals who occasionally or regularly travel or visit King's Cross.

#### Inclusion criteria

Registered on the King's Cross community smartphone application.App users living, working, or have previously visited King's CrossConsented to receiving email communications during their smartphone app sign-up

#### Exclusion criteria

Users of the King's Cross community smartphone app who have not given consent to receive email communication about the neighbourhood.

### Sample size

2.4

The sample size for this study was fixed at 4,809 individuals, representing the total number of users in the King's Cross Equiem database who met the eligibility criteria. Power analysis was conducted to evaluate the study's ability to detect differences between the three incentive conditions under varying levels of willingness to participate in the control group. Because the total N was fixed by the sampling frame, results are presented as minimum detectable differences (MDEs) in percentage points for each assumed control rate (29). Power for differences in proportions was calculated using standard two-sample methods for binary outcomes (30).

Due to limited directly comparable external estimates of baseline participation without incentives in similar digital-based recruitment contexts, a plausible range of control proportions (1%–70%) was assumed and used as a sensitivity analysis. Because EMA recruitment can yield single-digit participation rates in some settings (23), MDEs for low baseline proportions (1%–10%) are included within this range as part of the same fixed-N sensitivity framework. Power calculations were then conducted for each assumed proportion, using a Bonferroni-adjusted significance level of 0.01667 (0.05/3) to maintain a family-wise error rate of 0.05 across the three planned pairwise comparisons among the three conditions (31). Table 2 summarizes the assumptions and the corresponding minimum detectable differences.

**Table 2 T2:** Results of power analysis for detecting differences in willingness to participate across incentive conditions.

N	Proportion willing in control	Percentage point difference
4,809	0.01	1.16
4,809	0.02	1.53
4,809	0.03	1.81
4,809	0.04	2.04
4,809	0.05	2.24
4,809	0.06	2.41
4,809	0.07	2.57
4,809	0.08	2.72
4,809	0.09	2.85
4,809	0.10	2.97
4,809	0.20	3.86
4,809	0.30	4.36
4,809	0.40	4.61
4,809	0.50	4.66
4,809	0.60	4.52
4,809	0.70	4.18

With a fixed sample size of 4,809 and using the adjusted alpha for planned pairwise comparisons described above, the study would have approximately 80% power to detect absolute differences in willingness to participate of a few percentage points, depending on the assumed control proportion (Table 2). For example, if 30% of individuals in the control group were willing to participate, there would be sufficient power to detect an increase of 4.36 percentage points, corresponding to a willingness rate of 34.36% in an incentive condition. By contrast, if baseline willingness is in the single-digit range, detecting smaller absolute increases (e.g., 2 percentage points) with 80% power at *α* = 0.01667 would require a substantially larger sample per group than was available under the fixed sampling frame. These MDE benchmarks will be used to interpret observed effects under the predetermined sampling frame. If baseline willingness is in the single-digit range, smaller absolute effects may not be detected reliably; accordingly null findings will be interpreted relative to the corresponding low-rate MDE. These detectable differences provide a transparent benchmark for interpreting effects under the predetermined sampling frame.

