#### Sequence generation

2.7.1

Participants were randomized into three incentive groups (financial incentive, non-financial incentive, or no incentive) using a stratified block randomization procedure. Stratification was based on participant type within the Equiem communication platform (residents, visitors, and commercial occupiers). Randomization lists were generated using the Sealed Envelope online randomization service, which employed randomly permuted block sizes of 3, 6, and 9 to ensure a balanced allocation across incentive groups within each stratum. Sealed Envelope is a web-based clinical trial randomization platform that generates allocation sequences based on user-specified parameters (e.g., allocation ratio, stratification variables, and randomly permuted block sizes) and allows the sequence to be exported for implementation (33). The platform provides documentation on permuted-block and stratified randomization procedures, supporting transparent reporting and reproducible sequence generation. The randomization lists were generated by the researcher prior to participant assignment and without access to any identifying information (e.g., names or email addresses) stored on the Equiem platform.

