#### Primary outcome analysis

2.12.1.

The primary outcome is willingness to participate (Yes/No), operationalized as submission of a completed core questionnaire and valid email address (“Yes”) vs. not registering interest (selecting the non-interest option or not selecting either option). The effect of incentive type (financial, social, or no incentive) on willingness to participate will be evaluated using logistic regression. The model will include incentive condition as the main predictor and residential status (residents, workers, visitors) as a covariate, consistent with the stratification used during randomization. Odds ratios (OR) with 98.33% confidence intervals (CI) will be reported to compare each incentive group with the control group. A two-tailed *p*-value of < 0.01667 will be considered statistically significant (Bonferroni-adjusted to control the family-wise error rate at 0.05 across the three planned pairwise comparisons). In addition to odds ratios, marginal risk differences (RD) will be estimated to enhance interpretability.

Predicted probabilities will be obtained from the fitted logistic model through marginal standardization and RDs will be computed as the absolute difference in these marginal probabilities between groups. Confident Intervals (95%) will be derived using robust standard errors or nonparametric bootstrap methods, as appropriate. Primary inferences for the three pairwise comparisons of incentive type on the primary outcome will use 98.33% confident intervals (CIs) to adjust for multiple comparisons. Exploratory subgroup analyses and complementary RD estimates use 95% CIs and will be interpreted as estimation rather than confirmatory hypothesis testing. Interaction terms in subgroup models will be evaluated at a two-tailed alpha level of 0.05 and results will be reported as exploratory findings. In addition to the frequentist primary analysis, Bayes factors will be calculated to complement interpretation of the primary outcome by quantifying evidence for differences between incentive conditions.

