## Discussion

3

Recruiting participants into ecological momentary assessment (EMA) studies remains a persistent barrier to scalability, especially when protocols require frequent prompts over sustained periods (7, 9). This protocol addresses a practical methodological gap by using a randomized controlled trial (RCT) to test two scalable recruitment strategies at the point of invitation: (i) a probabilistic financial incentive (prize draw for limited-value shopping vouchers) and (ii) a social incentive (an invitation to a community research feedback event). By experimentally comparing these approaches against a no-incentive control, the study will generate causal evidence on whether uncertain financial rewards or socially meaningful engagement opportunities are more effective in motivating enrollment into smartphone-based well-being research conducted in real-world community settings.

Another contribution is the study's focus on heterogeneity in recruitment effects. Stratified randomization by participant type, together with planned subgroup analyses by age and gender, will help identify whether incentive responsiveness differs across segments of the local population. This is important because recruitment strategies can unintentionally amplify participation biases if they preferentially attract particular groups. The study therefore has the potential to inform more inclusive recruitment frameworks—for example, if some groups are more responsive to collective recognition and social affiliation, whereas others prioritize immediate or tangible material benefit.

The study will also generate evidence on non-participation by systematically documenting reasons for declining. Understanding non-enrollment is critical because barriers such as perceived burden, privacy concerns, low perceived personal benefit, or lack of trust can be addressed through concrete design and communication changes. These data can guide more user-centered invitations and study procedures, improving transparency and reducing avoidable friction at the point of decision.

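### Section 2.4 indexes the detectable differences for all three comparisons to the control rate; for financial versus social at low uptake that benchmark is too small if the weaker incentive also works

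*Protocol article*

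**What the plan says.** The trial has three arms and a total size set by the sampling frame: "The sample size for this study was fixed at 4,809 individuals". The Sample size section presents its power analysis as covering differences between the three incentive conditions. It works at the Bonferroni level of 0.01667, chosen "to maintain a family-wise error rate of 0.05 across the three planned pairwise comparisons among the three conditions". Table 2 lists one detectable difference for each assumed proportion willing in control, from 1% to 70%, and no other rate appears in it. The text concludes that "the study would have approximately 80% power to detect absolute differences in willingness to participate of a few percentage points, depending on the assumed control" rate, and illustrates this with 30% in control against 34.36% in an incentive arm. It adds that if baseline willingness is in single digits, null findings will be read against the low-rate MDE.

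The Primary outcome analysis section treats all three contrasts as primary: "Primary inferences for the three pairwise comparisons of incentive type on the primary outcome will use 98.33"% confidence intervals. The Discussion says the trial, by comparing both approaches with a no-incentive control, will show "whether uncertain financial rewards or socially meaningful engagement opportunities are more effective in motivating enrollment".

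**The concern.** Financial versus social is one of the three comparisons for which alpha was divided, so the general 80% statement appears to cover it. But the control arm supplies no data to that comparison. Its detectable difference depends on the two incentive-arm rates, and the lower of these exceeds the control rate whenever the weaker incentive works. Binomial variance rises with the rate up to 50%, so at low uptake a given gap is harder to detect between two raised rates than between control and one raised rate.

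What is at stake is interpretation. If both incentives raise uptake from a single-digit baseline and the head-to-head comparison is null, the plan's rule judges that null against a difference that the comparison had clearly less than 80% power to detect. The protocol itself expects that single-digit rates are possible, and that is where the mismatch is largest.

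**Working it through.** **Inputs.** Total N 4,809 (Sample size). Three arms: "This is a three-arm superiority randomised controlled trial (RCT"). Equal allocation is inferred from "randomly permuted block sizes of 3, 6, and 9 to ensure a balanced allocation across incentive groups within each stratum", giving 4,809/3 = 1,603 per arm. Alpha is 0.05/3, two-tailed (Sample size; Primary outcome analysis), so z = 2.394. Non-responders count as not willing, so there is no loss of N.

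**Formula.** For rates p1 < p2, n per arm and mean rate p̄ = (p1 + p2)/2:

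power = Φ{ [(p2 − p1) − z·√(2p̄(1−p̄)/n)] / √([p1(1−p1) + p2(1−p2)]/n) }

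The MDE at p1 is the difference that gives 80%.

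**Step 1: reproduce the plan's figure.** For 30% versus 34.36%, p̄ = 0.3218.
- n = 2,404.5: the null standard error is 0.01347 and z times it is 0.03225. Power = Φ[(0.0436 − 0.03225)/0.01346] = 80.0%.
- n = 1,603: the null standard error is 0.01650 and z times it is 0.03950. Power = Φ[(0.0436 − 0.03950)/0.01648] = 59.8%.

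All 16 rows of Table 2 match to two decimals with 2,404.5 per group, that is 4,809/2. With 1,603 per arm the printed differences give about 60% in every row, even against control. This is a separate error, but it decides which figures can be used below.

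**Step 2: the indexing problem in the table's own rows.** This needs no recalculation.
- Control 1%, weaker incentive up by the printed 1.16 points to 2.16%: the 2% row already asks for 1.53 points, not 1.16.
- Control 5%, weaker incentive up by 2.24 to 7.24%: the 7% row asks for 2.57, not 2.24.

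**Step 3: size with 1,603 per arm.** First recompute the MDE, d, at the control rate. Then compute financial-versus-social power for a gap of d, with the weaker incentive either d or d/2 above control. How far the weaker incentive exceeds control is an assumption, since the documents give no figure.

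| Control rate | d at 1,603 per arm (points) | Power, weaker incentive +d | Power, weaker incentive +d/2 |
|---|---|---|---|
| 1% | 1.50 | 50% | 63% |
| 2% | 1.94 | 56% | 67% |
| 3% | 2.28 | 59% | 69% |
| 5% | 2.80 | 64% | 71% |
| 10% | 3.69 | 69% | 74% |
| 30% | 5.36 | 77% | 78% |
| 40% | 5.65 | 79% | 79% |
| 50% | 5.70 | 81% | 80% |
| 70% | 5.10 | 86% | 83% |

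If the weaker incentive has no effect, power is 80% in every row.

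Worked row, control 5%: the weaker incentive is at 7.80% and the stronger at 10.60%, so p̄ = 0.092. The null standard error is 0.01021 and z times it is 0.02444. Power = Φ[(0.0280 − 0.02444)/0.01020] = 64%. The difference detectable with 80% power from 7.80% is 3.34 points rather than 2.80.

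**Step 4: the printed table as it stands.** At the printed differences, with the weaker incentive one printed MDE above control, financial-versus-social power is:
- 35% (control 1%), 40% (2%), 43% (3%) and 46% (5%) with the actual 1,603 per arm;
- 53%, 59%, 62% and 66% with the 2,404.5 per group that the table implies.

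The second line shows that the indexing problem exists whatever N is used. The first combines both errors.

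**The case against.** The text is openly anchored to control. The 80% is qualified by the assumed control proportion, the only worked example is incentive versus control, and Objective 2 and the odds ratios are framed against control. No sentence claims 80% for financial versus social by name. That is fair, but the same section says the analysis covers differences between all three conditions, sets alpha for three comparisons, and offers no other benchmark for the third.

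A reader could enter a correct table at the weaker incentive's rate. That is true, and it is the remedy; but the plan ties the reading of nulls to baseline willingness and does not tell the reader to do so.

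The size rests on a chosen scenario. At control 1% on the printed figures, one MDE per step means 1% to 2.16% to 3.32%, more than a tripling. This stands, which is why the half-MDE and zero-gain cases are shown as well.

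Three stronger readings are tempting but not supported:
- That power is overstated whenever the weaker incentive works. The loss is about one point at a 40% control rate and becomes a gain from about 50%, within Table 2's own range.
- That the plan would treat a null as proof that the two incentives work equally well. It says only that smaller effects may go undetected and that nulls are read relative to the MDE, and it adds 98.33% intervals and Bayes factors.
- That relabelling the printed table would be enough. Its figures give only about 60% power with 1,603 per arm even against control.

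**Conclusion.** The point holds in a limited form. The control-rate MDE is the wrong benchmark for financial versus social when control uptake is well below 50% and the weaker incentive raises uptake. With 1,603 per arm and correctly recomputed MDEs, the nominal 80% becomes about 50-69% for control rates of 1-10% if the weaker incentive gains one MDE, and about 63-74% if it gains half. At 30% the loss is about 2 to 3 points. These figures assume equal allocation, the pooled two-proportion test and a gap between the incentives equal to the control-indexed MDE.

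This is secondary to the per-group N error in Table 2, which affects all three comparisons, but correcting N alone would not remove it. The trial's data collection has ended, so what can change is how the head-to-head result is interpreted, not the design.

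**What to change.** 1. Recompute Table 2 with 1,603 per arm, for example 1.50 points at 1%, 2.80 at 5%, 3.69 at 10% and 5.36 at 30%. This must come first; otherwise the relabelled table still carries an 80% that does not hold.
2. Relabel the rate column as *proportion willing in the lower-rate arm of the comparison*.
3. State that the control-rate row applies to incentive versus control when the incentive raises uptake, and that a financial-versus-social result, including a null, is read from the row for the lower of the two incentive-arm rates. Example: 3.34 points rather than 2.80 when control is 5% and the weaker incentive is at 7.80%.
4. Give the power range for financial versus social at the control-indexed MDE together with its assumption: about 50-69% (weaker incentive gains one MDE) or 63-74% (half an MDE) for control rates of 1-10%, and no shortfall with no gain.

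The cost is a recomputed table, a changed column label and two or three sentences. Neither the design nor the primary model changes, but the stated sensitivity becomes less favourable.

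### Table 2's detectable differences fit two groups of about 2,404, not three arms of 1,603, so their power is about 60%, not 80%

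*Protocol article*

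**What the plan says.** The design is stated consistently. Section 2.1: "This is a three-arm superiority randomised controlled trial (RCT". Section 2.4: "The sample size for this study was fixed at 4,809 individuals". Section 2.7.1 describes "randomly permuted block sizes of 3, 6, and 9 to ensure a balanced allocation across incentive groups within each stratum", which is 1:1:1 allocation.

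Section 2.4 describes a two-sample calculation for binary outcomes, "using a Bonferroni-adjusted significance level of 0.01667 (0.05/3) to maintain a family-wise error rate of 0.05 across the three planned pairwise comparisons". Table 2 then gives one detectable difference for each control rate from 1% to 70%. Its only sample-size column is the total, 4,809; no per-group n is shown.

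The text below the table states that "the study would have approximately 80% power to detect absolute differences in willingness to participate of a few percentage points" and gives an example at a 30% control rate: "there would be sufficient power to detect an increase of 4.36 percentage points, corresponding to a willingness rate of 34.36% in an incentive condition". It adds that the tabulated values will serve as benchmarks for interpreting observed effects, and that null findings at single-digit rates will be read against the matching low-rate row.

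**The concern.** Alpha was divided by three because there are three pairwise comparisons among three arms. The total sample should likewise have been divided by three to get the n in each comparison, but the printed differences look too small for 1,603 per arm.

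If so, the only power statement in this article overstates the trial's sensitivity in every row. A true effect equal to a printed value would be missed about 40% of the time, not 20%. A non-significant result set against Table 2 would then be taken as stronger evidence against an effect than the trial can give. The proportional error is largest at the lowest control rates, and the single-digit range is where the article says it will lean on the table.

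**Working it through.** **Inputs, all from the protocol article**

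- Total N = 4,809, fixed (section 2.4).
- Three arms, balanced allocation (sections 2.1 and 2.7.1): 4,809/3 = 1,603 per arm, give or take a few for incomplete blocks within strata.
- Alpha = 0.05/3 = 0.01667 per comparison (section 2.4), two-tailed (section 2.12.1): z = 2.394.
- Power 80% (section 2.4): z = 0.842.
- No loss of outcome data: non-responders are coded as not willing (section 2.9.1), so everyone randomised is analysed.

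**Formula** (two-proportion z-test, pooled variance under the null). With control rate p1, incentive rate p2 = p1 + d, mean rate m = (p1 + p2)/2 and n per group:

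power = Φ{ [d − 2.394·√(2m(1−m)/n)] / √([p1(1−p1) + p2(1−p2)]/n) }

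**Step 1: the worked example, 30% against 34.36%.** Here d = 0.0436, m = 0.3218, 2m(1−m) = 0.4365 and p1(1−p1) + p2(1−p2) = 0.2100 + 0.2255 = 0.4355.

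- n = 2,404.5: (0.0436 − 2.394 × 0.01347)/0.01346 ≈ 0.843, so power = 80.0%. This is the article's figure.
- n = 1,603: (0.0436 − 2.394 × 0.01650)/0.01648 ≈ 0.248, so power = 59.8%.
- n needed per arm for 80% power at 4.36 points: (2.394 × √0.4365 + 0.842 × √0.4355)² / 0.0436² ≈ 2,403.

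**Step 2: all rows.** The formula was solved for the d that gives 80% power, in percentage points:

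| Control rate | Printed | n = 2,404.5 per group | n = 1,603 per arm | Power at printed value, 1,603 per arm |
|---|---|---|---|---|
| 1% | 1.16 | 1.164 | 1.50 | 59.5% |
| 2% | 1.53 | 1.530 | 1.94 | 59.8% |
| 3% | 1.81 | 1.807 | 2.28 | 59.9% |
| 4% | 2.04 | 2.037 | 2.55 | 59.9% |
| 5% | 2.24 | 2.236 | 2.80 | 59.9% |
| 6% | 2.41 | 2.412 | 3.01 | 59.7% |
| 7% | 2.57 | 2.572 | 3.20 | 59.7% |
| 8% | 2.72 | 2.717 | 3.38 | 59.9% |
| 9% | 2.85 | 2.851 | 3.54 | 59.7% |
| 10% | 2.97 | 2.975 | 3.69 | 59.6% |
| 20% | 3.86 | 3.860 | 4.76 | 59.8% |
| 30% | 4.36 | 4.358 | 5.36 | 59.8% |
| 40% | 4.61 | 4.609 | 5.65 | 59.8% |
| 50% | 4.66 | 4.659 | 5.70 | 59.8% |
| 60% | 4.52 | 4.522 | 5.52 | 59.7% |
| 70% | 4.18 | 4.184 | 5.10 | 59.7% |

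The third column matches the printed column throughout. The size of the gap is as expected: 2,404.5/1,603 = 1.5 and √1.5 ≈ 1.22. It widens to 1.497/1.16 ≈ 1.29 at a 1% control rate, where the variance rises quickly with p2. The n per arm that would give the printed values 80% power is 2,397 to 2,419 across rows, or about 7,200 in three arms.

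**Step 3: other settings that might explain the table.** At 1,603 per arm and a 30% control rate (printed 4.36):

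| Variant | Detectable difference |
|---|---|
| Alpha 0.05, two-sided | 4.63 |
| Alpha 0.05, one-sided | 4.10 |
| Alpha 0.01667, one-sided | 4.91 |
| Continuity correction | 5.42 |
| Unpooled variance | 5.35 |
| Arcsine | 5.36 |
| One arm against the other two pooled (1,603 v 3,206) | 4.64 |

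None gives 4.36. Even with no multiplicity correction (two-sided alpha 0.05), power at the printed differences is about 75%.

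**Step 4: what this does to interpretation.** At a 3% control rate the printed 1.81 implies that a true 2-point gain is detected with more than 80% power. At 1,603 per arm the power for that gain is 69%.

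**The case against.** Three points can be made for the plan.

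First, the two-way split is an inference, because the article prints no per-group n. That is true, but agreement on 16 rows from 1% to 70% leaves little doubt. The conclusion does not depend on the cause either: whatever was entered, the printed differences do not have 80% power with three arms of 1,603.

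Second, the practical damage is limited. N was set by the sampling frame, the trial ended on 30 November 2024, and no estimate, p-value or 98.33% confidence interval depends on Table 2. Those intervals will show the real precision. Section 2.4 also warns that small effects at single-digit rates may be missed. All of this stands, and it confines the error to interpretation. But the warning sends the reader back to the same understated rows, and the article commits to using them for null findings.

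Third, the corrected figures are approximations. The formula ignores adjustment for residential status, which the primary model includes, and at a 1% control rate (about 16 expected events per arm) the normal approximation is rough. This is a reason not to over-read the second decimal. It does not account for a shortfall of about 20 percentage points in power in every row.

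No section plans a two-group or pooled-arm comparison that would justify 2,404 per group.

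**Conclusion.** The error is confirmed and should be corrected. Under the trial's own design, every difference in Table 2 and the 30% to 34.36% example has about 60% power (59.5% to 60%, with pooled or unpooled variance), not 80%. The differences with 80% power are 22% to 29% larger than printed.

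This rests on equal allocation, two-sided alpha 0.01667 per comparison, the standard unadjusted two-proportion test, and all 4,809 invitees being analysed. Each is stated in or follows from the article. The separately published analysis plan was not available, so the finding concerns the figures in this article.

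**What to change.** 1. Recompute Table 2 with 1,603 per arm, using the fourth column of the table above, and add a column for n per arm.
2. Replace the worked example with a difference of 5.36 points, that is 30% against 35.36%.
3. State that the values are approximate, from an unadjusted two-proportion test at two-sided alpha 0.01667.
4. Use the corrected values wherever the benchmark is applied, including the reading of null findings in the results paper.

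Keeping the printed differences and restating their power as about 60% would also be accurate, but it fits the purpose less well, because the article uses the table as an 80% power benchmark.

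The cost is one table, one example and a sentence. Design, data and analysis are unchanged; the stated sensitivity becomes less favourable.
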